### Study Recruitment and Informed Consent

For MAP-U, potential participants in Ukraine will be informed about the study and recruited by email sent through the electronic database REDCap. Depending on the participation rate, non-responders will be contacted by means of Telegram and phone calls. All potential participants will be provided in REDCap with a video in Ukrainian which includes all relevant information regarding the purpose of the study, study procedures, and institutions involved, and the information of a professional hotline number were persons can find psychological support in case they are emotionally stressed by completing the questionnaire.

Recruitment of participants for both populations in MAP-Z (Ukrainian refugees and general population of Zurich) will be performed similarly. The randomly selected individuals will be informed about the study and recruited via postal mail. The letter will contain information about the study, an invitation to participate and a personalised access code to access REDCap. In REDCap, they will also be provided with a similar video as MAP-U (both in Ukrainian for refugees and German for the general population). Potential participants in both studies will also be able to access a PDF version of the detailed study participant information form.

Those interested will provide their informed consent to participate in the study electronically via REDCap and will be directly forwarded to fill the baseline assessment questionnaires.

### Baseline Assessment

At baseline, primary and secondary outcomes are assessed. Additional information collected through the baseline questionnaire includes oblast, contact information, and sociodemographic information including age, sex, citizenship, marital status, total number of people living in household, household income, residential situation, proximity to combat zone (i.e., previously occupied vs. never occupied, far from or close to combat zone) and details on migration processes and war-related experiences. Additionally, data on pre-existing health conditions including the presence of physical and mental health conditions and health behaviours (e.g., smoking, physical activity, and access to healthcare) will be collected.

### Follow-Up Assessments

Follow-up assessments will take place every 3 months for at least 2 years and include all primary endpoints and selected secondary endpoints.

### Statistical Analysis Plan and Sample Size Calculation

#### Statistical Methods

We will use medians and interquartile ranges or absolute numbers and percentages for the descriptive analyses. For prevalence estimates, there is the risk of overestimation if based on raw numbers since the cut-offs of instruments to classify into mental health condition (yes, likely) are optimized for sensitivity and screening for mental health conditions and thus include varying extent of false-positives. A recent systematic review indicated that prevalence estimates based solely on standardized instruments are about double as high as prevalence estimates based on standardized diagnostic interviews [18]. We will take this challenge into account in different ways: First, we will provide prevalence estimates and 95% credible intervals using a Bayesian logistic regression model adjusted for age-group and cluster of oblasts taking sensitivity and specificity of the instruments, as described above, and their uncertainty into account [33, 34].

We will conduct these analyses for the entire study population and also estimate prevalence of the four mental health conditions for subgroups as defined by cluster of oblasts (see above), age group and sex. The same applies to the analyses of aims 2 (impact of mental health on general health and healthcare seeking behaviour) and 3 (needs, preferences, barriers, and facilitators for mental healthcare services) where it is critical to gain an understanding of differences across subgroups. To assess factors (cluster, age, sex, sociodemographic variables, war-related experiences) associated with alcohol use disorder, abuse, anxiety, depression, or PTSD as well as with general health and healthcare seeking behaviour and needs, preferences, barriers, and facilitators for mental healthcare services we will use regression models while carefully adjusting for potential confounders. We will also consider clustering approaches to identify subgroups of the population with specific mental health burden and healthcare and social support needs. We will conduct all analyses in R, using the most current version at time of analysis https://www.r-project.org/.

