### Study Objectives

The main goal of the MAP program is to implement an agile, digital surveillance of public mental health in adult people living in different parts of Ukraine and in Ukrainian refugees living in the Canton of Zurich, Switzerland. The specific objectives are: (1) to determine the prevalence of symptoms of PTSD, depression, anxiety, and alcohol use disorder (a) at the beginning of the surveillance, and (b) up to at least 2 years; (2) to determine short-term and long-term temporal developments of mental health in the Ukrainian general population (in Ukraine and in the Canton of Zurich) and subgroups defined by age and level of war-related exposure; (3) to assess how mental health impacts general health and healthcare seeking behaviour; and (4) to assess needs, preferences, barriers, and facilitators for mental healthcare services of the Ukrainian general population and subgroups.

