Upon enrolment, participants will complete the baseline assessment through a secure digital study platform (REDCap) [14, 15]. To access REDCap for the baseline and follow-up assessments, randomly selected persons in Ukraine will receive an email (automated, including reminders) containing a link to the respective assessment. If there is no response, we will approach them via Telegram or phone calls. For MAP-Z, the initial contact will be established by postal mail which has been proven to be a successful way in other population-based studies. Follow-up assessments, where participants will be invited by email or Telegram, will take place every 3 months for at least 2 years. The study design thus follows that of the digital cohort of Corona Immunitas, the COVID-19 Social Monitor and the Swiss MS Registry [16, 17]. Such a digital approach has the advantage of being independent from geography, thereby increasing the catchment area of interest [16, 17]. Participants from the Ukrainian population who are unable to fill out the questionnaires online are offered to complete the questionnaire through a phone interview (MAP-U only). As with the COVID-19 social monitor, results from MAP will be displayed in almost real-time on an online platform, providing the public, policymakers and scientists with the opportunity to monitor the prevalence and trajectories of symptoms of PTSD, depression, anxiety, and alcohol use disorder among the general population and by relevant subgroups.

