### Primary Endpoints

The primary endpoints are the prevalence and incidence of symptoms of PTSD, depression, anxiety, and alcohol use disorder. Since we will not be able to establish diagnoses through mental healthcare experts (psychiatrists or psychologists) according to the International Classification of Disease (ICD)- 10/11, or the Diagnostic and Statistical Manual of Mental Disorders (DSM)- 5, we rely on commonly used, standardized questionnaires which we selected following a systematic selection process [18]. For the four mental health conditions of interest, we identified potential instruments and compared them against our selection criteria: (a) should have strong psychometric properties (construct validity, internal consistency reliability, test-retest reliability, and ability to detect change over time) to capture symptoms; (b) estimates of sensitivity and specificity are available (c) can be implemented in digital surveillance (i.e., can be completed independently by participants); (d) are available in the Ukrainian language; (e) are appropriate in the context of the war in Ukraine; (f) have established cut-offs for the presence or likely presence of the four conditions of interest; (g) are or have been used in other population-based studies; (h) are short in duration or low burden to complete; (i) have been previously used in Ukraine. Instruments were discussed and final decisions made at an international working group meeting held in Zurich in Spring 2023.

Based on the criteria mentioned above, we selected the Posttraumatic Stress Disorder Checklist (PCL-5) for the assessment of PTSD, Patient Health Questionnaire (PHQ-9) for depression, generalized anxiety disorder 7 (GAD-7) for anxiety, and Alcohol Use Disorders Identification Test (AUDIT) for the alcohol use disorder. References for each of the instruments regarding the validation of psychometric properties (in a general non-Ukrainian population), the translation process into Ukrainian, and validation and/or utilisation in the Ukrainian population are provided in Table 1. Furthermore, the selected instruments are aligned with those used by the Global Burden of Disease (GBD) from The Institute for Health Metrics and Evaluation.

**TABLE 1 T1:** Mental Health Assessment of the Population, Switzerland, 2024

Instrument	Sensitivity %/Specificity % (score of instrument as cut-off)	Psychometric properties	Translation process	Validation/utilisation in Ukraine

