#### Sample Size Considerations and Calculation

We expect a prevalence of 15% for alcohol use disorder, 25% for anxiety and depression and 40% for PTSD in the Ukrainian population based on the available prevalence data in Ukraine and on data from other conflict areas [11]. Sample size requirements are highest for a prevalence of 40%, on which we thus base sample size calculations. We consider a specific age group in a specific cluster (e.g., participants 25–44-year-old in a specific cluster of oblasts) as the unit for which we need a certain precision to estimate prevalence. To provide a precision of ±5% in estimating prevalence with 95% confidence intervals for a specific age group in a specific cluster, the required sample size is 369 survey respondents per combination of age group and cluster. Assuming a potential attrition of 15% among those who consent to participate, the required sample size for enrolment is 435 per age and cluster stratum. The size of the target sample is 5,220 persons (net sample; given 4 age and 3 cluster of oblasts strata). Considering a participation rate of approximately 7% for MAP-U, reflecting the difficult situation in Ukraine, the final number to be randomly drawn from the population registry in Ukraine is 1,740 per stratum and 74,570 for the total sample, respectively. For the MAP-Z study, a participation rate of 25% is assumed based on experiences with previous population-based studies in the canton of Zurich (e.g., Corona Immunitas studies). For the age groups of 25–44 and 45–64 years in people living with protection status S as well as for all four age groups of the general population of the canton of Zurich we will also have 435 participants per age group, or 1,740 people to be invited initially. But there are less than 1,740 people with protection status S in the youngest (18–24 years) and oldest (65+ years) age group with protection status S in Zurich. Thus, we will aim for randomly selecting 684 people in those two age groups in order to have 171 (25%) finally included. In these age groups, the precision will be lower, and 95% CI expected at ±8%. The total sample sizes for people living with protection status S and for the general population living in the canton of Zurich will thus be 1220 and 1740, respectively.

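### The one prevalence model stated adjusts for age group and cluster; applied to follow-up waves, it would let symptom-related dropout within those cells appear as change in population mental health

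*Protocol article*

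**What the plan says.** The Primary Endpoints section states: "The primary endpoints are the prevalence and incidence of symptoms of PTSD, depression, anxiety, and alcohol use disorder". The Follow-Up Assessments section sets the schedule: "Follow-up assessments will take place every 3 months for at least 2 years and include all primary endpoints". Objective 2 is "to determine short-term and long-term temporal developments of mental health in the Ukrainian general population" and its subgroups, and objective 1(b) asks for prevalence up to at least 2 years. Under Study Design, "results from MAP will be displayed in almost real-time on an online platform", for use by the public, policymakers and scientists.

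For prevalence, Statistical Methods names one model: a "Bayesian logistic regression model adjusted for age-group and cluster of oblasts taking sensitivity and specificity of the instruments" into account, with their uncertainty. Prevalence is also to be reported by cluster, age group and sex. Sociodemographic variables and war-related experiences appear in the same section, but in the regression models for associated factors.

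Attrition enters the sample size: "the required sample size is 369 survey respondents per combination of age group and cluster", and "Assuming a potential attrition of 15% among those who consent to participate", "the required sample size for enrolment is 435 per age and cluster stratum". Study Design adds automated reminders for the baseline and follow-up assessments in Ukraine, then Telegram or phone contact for those who do not respond, and a phone interview for those who cannot answer online.

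**The concern.** A cohort that is followed and not redrawn becomes, wave by wave, the subset that still answers. A model that conditions on age group and cluster treats those who stop and those who continue within a cell as having the same prevalence. If people with symptoms stop sooner, the curve falls without any recovery. If people who are well lose interest sooner, it rises without any deterioration.

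The Discussion intends the results to steer resource allocation and service planning, so apparent change of this kind could be acted on. The bias also does not shrink as the sample grows, so it weighs most in national curves, where sampling error is smallest. The correction for sensitivity and specificity addresses a different error and does not act on dropout.

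**Working it through.** **The plan's own figures**

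Inputs from Sample Size Considerations and Calculation: prevalence p = 0.40 (PTSD), precision 0.05, 95% confidence, attrition 15%, 4 age groups × 3 clusters.
- Respondents: 1.96² × 0.40 × 0.60 / 0.05² = 368.8, so 369.
- Enrolment: 369 / 0.85 = 434.1, so 435.
- Total: 435 × 12 = 5,220.

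All three reproduce. The sizing therefore expects about 369 responders per stratum after attrition, or 0.85 × 5,220 = 4,437 nationally.

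**Effect of selective dropout when nothing changes**

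Let A be attrition, d1 and d0 the dropout probabilities in cases and non-cases, and OR the ratio of their dropout odds. The OR is not in the documents; it is assumed and varied. Solve

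0.40·d1 + 0.60·d0 = A, with d1/(1 − d1) = OR × d0/(1 − d0).

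Prevalence among responders is 0.40 × (1 − d1)/(1 − A).

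| A | OR (cases v non-cases) | d1 | d0 | Responders' prevalence | Shift (points) |
|---|---|---|---|---|---|
| 15% | 1.5 | 18.2% | 12.9% | 38.5% | −1.5 |
| 15% | 2 | 20.4% | 11.4% | 37.4% | −2.6 |
| 15% | 1/1.5 | 12.0% | 17.0% | 41.4% | +1.4 |
| 30% (assumed) | 1.5 | 35.2% | 26.6% | about 37.0% | −2.9 |
| 30% (assumed) | 2 | 38.8% | 24.1% | about 35.0% | −5.0 |

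**The misclassification correction leaves the shift in place**

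Take the second row, with sensitivity and specificity both 0.94. The apparent prevalence is 0.374 × 0.94 + 0.626 × 0.06 = 0.389. The corrected value is (0.389 − 0.06)/0.88 = 0.374, the same 37.4%.

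**Yardstick**

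- National half-width, uncorrected: 1.96 × √(0.24/4,437) = 0.0144, or 1.44 points.
- After the PCL-5 correction at fixed sensitivity and specificity: apparent prevalence 0.40 × 0.94 + 0.60 × 0.06 = 0.412, and 1.96 × √(0.412 × 0.588/4,437)/0.88 = 0.0165, or 1.65 points.
- Both treat the sample as a simple random one.

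At 15% attrition, odds of 2 in cases (−2.6) lie clearly outside both half-widths. Odds of 1.5 in cases (−1.49) lie just outside the first and inside the second. Odds of 1.5 in non-cases (+1.41) lie just inside the first. All three are within the 5-point stratum precision.

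**Check of the cell adjustment and the remedy**

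A simulation used 12 strata of 435, true prevalence from 30% to 50% across strata, 15% attrition and 2,000 runs. Here the ratio of dropout probabilities, not odds, was 2. Estimates made stratum by stratum and averaged gave 37.0% against a true 40.0%. Weights from inverse retention by baseline status within each stratum gave 40.0%. That recovery assumes status does not change and dropout depends only on baseline status.

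**The case against.** The strongest objection is that no sentence prescribes an analysis of responders alone. The article states no wave-by-wave fit and gives no separate model for objective 2 or for incidence. It describes the analyses as covering the entire study population, and a fuller plan may add weights or a longitudinal model. This stands in part. A reader might infer that the plan has chosen a complete-case analysis, and the text does not support that. What it supports is narrower: the model it does state for prevalence, if used at follow-up, cannot remove symptom-related dropout within a cell.

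A reader might also infer that non-response is ignored apart from inflating the sample size. That is wrong, since the reminders and the Telegram and phone contact address it at collection. They may reduce selective loss but do not adjust the estimate for what remains.

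The 15% is stated among those who consent, with no time horizon. Consent precedes the baseline questionnaire, so some of the 15% may have no baseline scores. It cannot be said that every dropout has them, and weights cannot be computed for those who do not.

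Finally, the odds ratios and the 30% attrition are assumptions, and the planned precision is ±5 points per stratum, which the bias does not exceed at 15% attrition in the cases shown. This is correct and limits the concern mainly to national curves and to larger cumulative loss.

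**Conclusion.** The concern holds in conditional form. Used on follow-up waves, the stated prevalence model would pass dropout related to symptoms within an age-by-cluster cell into the trajectories as apparent change. With true PTSD prevalence constant at 40% and 15% attrition, the illustrations run from 37.4% (dropout odds 2 times higher in cases) to 41.4% (odds 1.5 times higher in non-cases). Against a national half-width of 1.44 to 1.65 points, only the former is clearly outside; odds of 1.5 in either direction are borderline. Loss beyond 15% over at least eight follow-up waves would enlarge the shift.

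A reader might conclude that the platform will show a false recovery. The documents do not support that, because they give neither the strength nor the direction of any link between symptoms and dropout. The figures rest on assumed odds ratios and on unchanged true prevalence. The corrected half-width also rests on fixed sensitivity and specificity, whereas the plan's interval will carry their uncertainty too.

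**What to change.** For each wave after baseline, define the estimate as prevalence among all participants who completed baseline. Obtain it by adding inverse-probability-of-response weights to the stated Bayesian model. The response model would use baseline and last observed symptom scores, age, sex, cluster, displacement and war exposure. An equivalent joint model over waves would also serve; it would need to allow for false positives recurring in the same person and to average over person-level effects to give population prevalence.

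Use the same estimate on the online platform. Beside each wave, show the baseline prevalence of that wave's responders and that of the full baseline cohort, so that users can see selection directly. Add a sensitivity analysis for dropout that depends on current symptoms, which weights built on past scores do not address. Report separately those who consented but did not complete baseline.

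No new data are needed, since the Baseline Assessment section already collects primary outcomes, sociodemographic data, migration details and war-related experiences. The costs are more programming, somewhat wider intervals and a remaining missing-at-random assumption given the observed scores, which is weaker than assuming equal prevalence among leavers and stayers within a cell.

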#### Sample Size Considerations and Calculation

We expect a prevalence of 15% for alcohol use disorder, 25% for anxiety and depression and 40% for PTSD in the Ukrainian population based on the available prevalence data in Ukraine and on data from other conflict areas [11]. Sample size requirements are highest for a prevalence of 40%, on which we thus base sample size calculations. We consider a specific age group in a specific cluster (e.g., participants 25–44-year-old in a specific cluster of oblasts) as the unit for which we need a certain precision to estimate prevalence. To provide a precision of ±5% in estimating prevalence with 95% confidence intervals for a specific age group in a specific cluster, the required sample size is 369 survey respondents per combination of age group and cluster. Assuming a potential attrition of 15% among those who consent to participate, the required sample size for enrolment is 435 per age and cluster stratum. The size of the target sample is 5,220 persons (net sample; given 4 age and 3 cluster of oblasts strata). Considering a participation rate of approximately 7% for MAP-U, reflecting the difficult situation in Ukraine, the final number to be randomly drawn from the population registry in Ukraine is 1,740 per stratum and 74,570 for the total sample, respectively. For the MAP-Z study, a participation rate of 25% is assumed based on experiences with previous population-based studies in the canton of Zurich (e.g., Corona Immunitas studies). For the age groups of 25–44 and 45–64 years in people living with protection status S as well as for all four age groups of the general population of the canton of Zurich we will also have 435 participants per age group, or 1,740 people to be invited initially. But there are less than 1,740 people with protection status S in the youngest (18–24 years) and oldest (65+ years) age group with protection status S in Zurich. Thus, we will aim for randomly selecting 684 people in those two age groups in order to have 171 (25%) finally included. In these age groups, the precision will be lower, and 95% CI expected at ±8%. The total sample sizes for people living with protection status S and for the general population living in the canton of Zurich will thus be 1220 and 1740, respectively.

This sample size provides 95% confidence intervals of ±6%–7% when analysing the results separately for women and men, age groups and cluster of oblasts. Sample size calculations were performed using the Scalex SP calculator [34].

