For the PHQ-9 we chose a cut-point of >=10 and assume a sensitivity of 0.88 and specificity of 0.88, as reported by Kroenke and colleagues [21]. The cut-point for the GAD-7 is >=10, the assumed sensitivity is 0.89 and specificity is 0.82 as reported by Spitzer et al. [23]. In the case of the AUDIT, we believe that the most applicable estimate of diagnostic validity was provided by Moehring et al. [25] based on a general population study in Germany. They observed a very similar AUDIT score distribution to the one in our population and, given a cut-point of >=5, reported a sensitivity of 0.65 and specificity of 0.85. The most applicable estimate for the diagnostic validity of the PCL-5 was provided by Geier et al. [19] which found that a cut-point of >=31 resulted in a sensitivity of 0.94 and a specificity of 0.94.

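### The ±5% precision and the choice of 40% as the most demanding case hold for the uncorrected screen-positive proportion, not for the misclassification-corrected prevalence that the plan will report

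*Protocol article*

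**What the plan says.** In the Protocol article, Sample Size Considerations and Calculation, the planning values are these: "We expect a prevalence of 15% for alcohol use disorder, 25% for anxiety and depression and 40% for PTSD in the Ukrainian population". The largest is taken as decisive: "Sample size requirements are highest for a prevalence of 40%, on which we thus base sample size calculations". The unit of precision is one age group within one cluster of oblasts, and for it "the required sample size is 369 survey respondents per combination of age group and cluster". With 15% attrition this becomes 435 enrolled per stratum and 5,220 over 12 strata. The same section gives ±8% for the two small refugee age groups (171 included in each) and ±6% to ±7% "when analysing the results separately for women and men, age groups and cluster of oblasts".

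The estimate to be reported is a different quantity. Primary Endpoints says that prevalence will be corrected for misclassification. Statistical Methods names a Bayesian logistic regression adjusted for age group and cluster, "taking sensitivity and specificity of the instruments, as described above, and their uncertainty into account". Primary Endpoints also fixes the accuracy values. The weakest pair is that of the AUDIT: "given a cut-point of >=5, reported a sensitivity of 0.65 and specificity of 0.85".

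**The concern.** Correcting a screen-positive proportion for misclassification divides its standard error by (sensitivity + specificity − 1). The precision figures contain no such term. The stated half-widths may therefore be too narrow for all four primary endpoints, and the endpoint used to set the sample size may be the wrong one, because the loss of precision is greatest for the instrument with the poorest accuracy and not for the condition nearest 50% prevalence.

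At stake is what readers expect of the stratum results. These are to be shown in near real time and used to allocate resources between regions and groups.

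**Working it through.** **Inputs.** From the sample size section: prevalence p = 0.40 (PTSD), 0.25 (depression), 0.25 (anxiety), 0.15 (alcohol use disorder); half-width 0.05; 95% confidence (z = 1.96); n = 369. From Primary Endpoints, Se/Sp: PCL-5 0.94/0.94, PHQ-9 0.88/0.88, GAD-7 0.89/0.82, AUDIT 0.65/0.85.

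**The plan's own figures.** n = z²p(1−p)/d² = 1.96² × 0.40 × 0.60 / 0.05² = 368.8, so 369. Then 369/0.85 = 434.1, so 435, and 12 × 435 = 5,220. For the small refugee groups, 1.96 × √(0.24/171) = 7.3%, or 8.0% if 15% attrition is also taken off (171 × 0.85 = 145). By sex, half a stratum (184.5 to 217.5) gives 7.1% to 6.5%. All the stated figures are reproduced with no sensitivity or specificity term.

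**Corrected estimate.** Expected screen-positive proportion: q = Se·p + (1−Sp)(1−p). Half-width: 1.96 × √(q(1−q)/n) / (Se+Sp−1). Required n: 1.96² × q(1−q) / [(Se+Sp−1) × 0.05]².

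For alcohol use disorder, q = 0.65 × 0.15 + 0.15 × 0.85 = 0.225. The half-width is 1.96 × √(0.225 × 0.775/369)/0.50 = 8.5%. The required n is 3.8416 × 0.174375/0.025² = 1,072.

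| Endpoint | Se+Sp−1 | q | Uncorrected, n = 369 | Corrected, n = 369 | Corrected, n = 435 | n for ±5% |
|---|---|---|---|---|---|---|
| PTSD | 0.88 | 0.4120 | 5.0% | 5.7% | 5.3% | 481 |
| Depression | 0.76 | 0.3100 | 4.4% | 6.2% | 5.7% | 570 |
| Anxiety | 0.71 | 0.3575 | 4.4% | 6.9% | 6.3% | 701 |
| Alcohol use disorder | 0.50 | 0.2250 | 3.6% | 8.5% | 7.8% | 1,072 |

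A simulation of the corrected estimate at n = 369 gave 5.7, 6.2, 6.9 and 8.4%. The ranking reverses: PTSD is the most demanding endpoint without correction, alcohol use disorder with it (1,072/369 = 2.9 times the planned number).

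**Other stated precisions.** By sex, with 217.5 to 184.5 respondents: PTSD 7.4–8.1%, depression 8.1–8.8%, anxiety 9.0–9.7%, alcohol use disorder 11.1–12.0%, against the stated 6–7%. At n = 171: 8.4% (PTSD) to 12.5% (alcohol use disorder), against the stated 8%.

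**If 15/25/40% are raw screen-positive rates.** The corrected prevalence is (raw + Sp − 1)/(Se+Sp−1). For alcohol use disorder this is (0.15 + 0.85 − 1)/0.50 = 0. PTSD, depression and anxiety have half-widths of about 5.7, 5.8 and 6.2% at n = 369.

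**Uncertainty in Se and Sp.** The article does not give the validation sample sizes, so these are assumptions. With 200 cases and 3,000 non-cases the half-widths at n = 369 become 5.9, 6.5, 7.2 and 9.0%. With 100 and 500 they become 6.3, 7.1, 8.1 and 10.4%.

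**The case against.** The strongest reply is that the planned estimator is not a stand-alone calculation in each stratum. Statistical Methods adjusts for age group and cluster. If that model is additive, 6 parameters describe 12 cells, and in a balanced layout the sampling variance per cell roughly halves. Multiplying the n = 369 half-widths by √(6/12) gives about 4.0, 4.4, 4.9 and 6.0% with sensitivity and specificity known. So a reader might infer from the table that ±5% is out of reach for every primary endpoint; the article does not support that, because three of the four could meet it under such a model. The reply does not rescue the text as written. The article does not say that the model is additive, the sample size section takes each age-by-cluster cell as its unit and uses a one-sample formula, and the uncertainty in sensitivity and specificity that the model also carries widens the intervals again.

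A reader might also infer that alcohol use disorder is the limiting endpoint whatever the planning values mean. That too is unsupported. If 15% is a raw rate, the corrected value sits at zero, where the symmetric formula (7.3%) does not apply. A credible interval with a flat prior and known accuracy runs from about 0.1% to 9.1%, a half-width of about 4.5%, narrower than for the other three endpoints. What follows on that reading is that the alcohol planning value cannot be used.

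Third, n is uncertain. All 435 enrolled may contribute at baseline. The Abstract gives 17,400 for Ukraine, which over 12 strata less 15% is 17,400/12 × 0.85 = 1,232 per stratum, enough for ±5% on all four endpoints in the table. But the sample size section sets 5,220, and 7% of the 74,570 to be drawn is also 5,220, so the precision claim as argued rests on 369.

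Last, the reported credible intervals will carry the misclassification themselves. The fault lies in the stated planning precision, not in the planned analysis.

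**Conclusion.** Wrong as written. The half-widths of ±5%, ±8% and ±6–7% describe the uncorrected screen-positive proportion, and the article commits to reporting something else. For a stand-alone stratum estimate at n = 369, the expected half-widths range from ±5.7% (PTSD) to ±8.5% (alcohol use disorder), and the premise that 40% prevalence sets the highest requirement fails.

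These figures rest on three assumptions: the planning prevalences are true prevalences, sensitivity and specificity are known, and strata are not pooled. Relaxing the second widens the intervals; relaxing the third narrows them. The figures are therefore neither a best case nor the exact widths the model will give. Under the raw reading, the size for alcohol use disorder cannot be stated from a planning value that corrects to zero.

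**What to change.** Keep the sample size and change the text in five places:

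1. State that ±5%, ±8% and ±6–7% apply only to the uncorrected screen-positive proportion.
2. Give expected half-widths per instrument for the corrected prevalence under the planned model, stating the n used, the assumed uncertainty in sensitivity and specificity, and any pooling across strata. The table above serves for the stand-alone case only.
3. Remove the sentence that 40% is the most demanding case, or limit it to the uncorrected proportion.
4. State whether 15/25/40% are raw or corrected. If raw, replace the alcohol planning value.
5. Reconcile the 17,400 in the Abstract with the 5,220 in the sample size section, since the precision depends on which is meant.

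The cost is a short recalculation and a less favourable stated precision. Sampling, endpoints and analysis do not change.
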